### Safety evaluation and adverse events

The safety evaluation mainly refers to the evaluation of safety indicators and adverse events. The safety indicators will be tested once before and after the treatment and will include a general physical examination (blood pressure, breathing, pulse), routine blood tests, routine urine tests, routine stool tests, electrocardiograms, and liver and kidney function tests. Adverse events in this study will be defined as any discomfort, symptoms, or diseases that occurred during this acupuncture clinical trial, such as fainting, allergies, or pain. If someone faints, researchers will immediately remove needles, then keep the patient in a supine position in a ventilated place, and give him/her warm water or sugar water to let him/her fully rest until the body recovers. If allergies or pain occurs, needles will be immediately withdrawn, and the patient will be treated symptomatically. All the above detailed information regarding safety evaluations will be reported in detail in case report forms (CRFs), and the impact of all adverse events will be analyzed at the end of the study. Participants who experience adverse events will be compensated accordingly.

### Data management

All information of participants will be truthfully, completely, accurately, and timely recorded in CRFs, and codes and initials will be used to replace the information of participants. Special personnel will be asked to manage the relevant data, and each participant’s personal information will be kept strictly confidential. Without the explicit permission of the person in charge of the research group, data will not be shared with third parties other than data recorders and data administrators. At the end of the trial, study participants will submit the CRFs on time, and then, the quality control team members will check the completeness and accuracy of the CRFs.

### Quality control

To guarantee the research quality of this trial, we will invite a qualified clinical trial expert from the Clinical Research Center of the First Affiliated Hospital of Henan University of Chinese Medicine to monitor this study, and detailed regulations for each link of data collection and management will be formulated to clarify the responsibilities of researchers. If any problems in the project are identified, the center will decide to change the research plan after approval by the application ethics committee. A reasonable and feasible data standard operating procedure (SOP) will be established to ensure quality at each stage of data collection and management. Data management will be carried out by relevant personnel who have been trained and operate strictly in accordance with the SOP. Meanwhile, a quality control team will be established to conduct quality control and inspections on a regular basis. The qualified clinical trial expert will monitor the work of the clinical trial center at least once a month.

### Statistical analysis

Statistical analysis of all data will be performed using SPSS 22.0 software by specialized statisticians who are not the principal researchers. Classified variables will be analyzed using Pearson’s *χ*^2^ test or Fisher’s exact test, and continuous variables will be evaluated using Student’s *t* test or an appropriate nonparametric method. The measurement data from different treatment groups will be statistically described by the mean ± standard deviation. When comparing within groups or between groups, a normality test and homogeneity of variance test will be performed before data analysis of each group. If the data satisfy the normal distribution and homogeneity of variance, then the *t* test will be used for comparison between two groups, and the LSD or SNK method will be used for multiple comparisons. Conversely, the rank-sum test will be used for nonnormality or nonuniformity of variance. The significance level used for statistical analysis with 2-tailed testing will be set at 5%.

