### Sample size

We will conduct this study using a randomized controlled trial design, and the main observed outcome will be improvements in patient cognitive function. Our previous small-sample (20 cases) clinical observation found that 2 weeks of EA plus routine cognitive rehabilitation treatment and EA plus NR and routine cognitive rehabilitation treatment can reduce scores on the MOCA scale by 3.17 ± 2.12 and 4.40 ± 2.59 points, respectively. With the significance test level set at 0.05 and the test power at 0.9, the sample size was calculated by using the following:
$$ N=2\times {\left[\left({z}_{\alpha /2}+{z}_{\beta}\right)\times \upsigma /\updelta \right]}^2 $$

*N* is the required sample size for each group, and the sample size of each group is equal. When *α* is 0.05 and *β* is 0.1, the normal distribution quantile table shows the following:
$$ {Z}_{\alpha /2}=1.96 $$

and
$$ {Z}_{\beta }=1.282. $$

*σ* and *δ* represent the larger standard deviation and the mean difference between two groups, which are 2.59 and 1.23, respectively. By substituting the above data into the formula, it was calculated that 93 patients will be needed in each group. Accounting for a 10% dropout rate, the final estimated sample size is approximately 103 patients in each group (206 in total).

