### Outcome measures

All participants will be evaluated at these time points: baseline, week 4, week 8, and follow-up week 12 and week 24 after all treatments are completed. All treatment evaluations will be conducted by researchers who will be blinded to the treatment allocation.

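### The sample size rests on the SD of MOCA change, but the analysis section names only an unadjusted two-group test, does not tie it to change, and leaves the baseline scores unused

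*Protocol article*

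**What the plan says.** **Sample size.** The planning values come from a 20-case, 2-week pilot in which the two regimens changed "scores on the MOCA scale by 3.17 ± 2.12 and 4.40 ± 2.59 points, respectively". The section takes improvement in cognitive function as the main outcome. Sigma and delta "represent the larger standard deviation and the mean difference between two groups, which are 2.59 and 1.23, respectively", and "With the significance test level set at 0.05 and the test power at 0.9" "it was calculated that 93 patients will be needed in each group". A 10% dropout allowance brings this to about 103 per group, 206 in all.

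**Outcome measures.** MMSE, MOCA and BI are assessed at "baseline, week 4, week 8, and follow-up week 12 and week 24 after all treatments are completed". Every patient should therefore have a baseline value on each scale.

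**Statistical analysis.** Continuous variables are compared by Student's t test or a nonparametric method. If normality and equal variance hold, the t "test will be used for comparison between two groups"; if not, a rank-sum test is used. Testing is two-sided at 5%. No covariate is named, and the section does not say whether the compared quantity is the score at a visit or its change from baseline.

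**The concern.** The SD behind the 93 per group is that of a within-patient difference, from which stable differences between patients have been subtracted. The stated power carries over only if the analysis also removes them, by testing change or by adjusting for baseline. The analysis section requires neither.

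This is more than detail left to an analysis plan. The section commits to a test, its assumption checks and its fallback, and the test it commits to is unadjusted. Two readings are open, with possibly very different power, and nothing in the text prevents the choice between them being made after the data are seen. Even on the better reading, the baseline scores are not used as efficiently as they could be.

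**Working it through.** **Inputs from the document.** Difference 1.23 (4.40 − 3.17); SD of change 2.59 (the larger of 2.12 and 2.59); two-sided alpha 0.05; power 0.90; 1:1 allocation; 93 evaluable per group.

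**Assumed, because the document does not give it.** The SD S of the MOCA score itself, taken from 2.59 to 6, and equal variance at baseline and follow-up.

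**1. The plan's own figure.** N = 2 × [(1.96 + 1.282) × 2.59 / 1.23]² = 93.2 per group. The stated 93 reproduces (94 if rounded up). Power at 93 per group is 89.9% by the normal approximation and 89.6% by the noncentral t. This is the power of an unadjusted t test on change.

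**2. Link between the two SDs.** With equal variances, SD(change)² = 2S²(1 − ρ), where ρ is the baseline-to-follow-up correlation. Hence ρ = 1 − 2.59² / (2S²). For S = 4: ρ = 1 − 6.708/32 = 0.79.

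**3. Unadjusted t test on follow-up scores.** The noncentrality is 1.23 / [S × √(2/93)] on 184 degrees of freedom. For S = 4: 1.23 / (4 × 0.1466) = 2.10, which gives 55% power.

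**4. ANCOVA on baseline.** The residual SD is S√(1 − ρ²). Substituting from step 2, this equals 2.59 × √[(1 + ρ)/2]. It cannot exceed 2.59, nor can it exceed S. Under equal variances, ANCOVA is therefore never less precise than either unadjusted test, apart from the one degree of freedom spent on the covariate. For S = 4: 4 × √(1 − 0.79²) = 2.45, which gives 93% power.

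Results at 93 per group, difference 1.23 (powers by t distribution; last column by the protocol's formula, rounded up):

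| Assumed S | Implied ρ | Power, t test on follow-up score | ANCOVA SD | Power, ANCOVA | n per group for 90%, t test on follow-up score |
|---|---|---|---|---|---|
| 2.59 | 0.50 | 90% | 2.24 | 96% | 94 |
| 3 | 0.63 | 79% | 2.34 | 95% | 126 |
| 4 | 0.79 | 55% | 2.45 | 93% | 223 |
| 5 | 0.87 | 39% | 2.50 | 92% | 348 |
| 6 | 0.91 | 28% | 2.53 | 91% | 501 |

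**5. The other side of the break-even.** At ρ = 0.5 the two unadjusted tests have the same power. Below it, testing follow-up scores does better than planned: at ρ = 0.4, S is 2.36 and power is 94%, against 97% for ANCOVA.

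**The case against.** The strongest reply is that there is no mismatch. The Sample size section speaks of improvement and uses a formula for comparing mean changes, so the natural reading of the t test is a test on change, which keeps about 90% power. A reader might infer from the silence on change that raw scores will be tested and that the trial really has 28% to 79% power. The document supports neither step. It does not name the analysed quantity, and it gives no SD for the MOCA score and no correlation. This stands, and it makes the power loss conditional.

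The size of the raw SD can be argued both ways. Entry is broad (age 30 to 75, disease course from 1 month to 1 year, MMSE cut-offs by educational level), which favours a spread above 2.59. Requiring impairment on both scales truncates the upper end at baseline. A raw SD above 2.59 on a 30-point scale is plausible, but it remains an assumption.

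Two more inferences go too far. The first is that unadjusted testing is invalid: in a 1:1 randomised trial it is unbiased with correct type I error, and chance imbalance is already reflected in its standard error. The second is that patients with a missing visit will be dropped by separate tests at each visit: the section does not set out such a scheme, and missing-data handling is commonly left to the full analysis plan.

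Finally, the ANCOVA figures carry a difference and an SD from a 20-case, 2-week pilot into an 8-week trial. A smaller difference or a larger SD of change would lower them. The same caveat applies to the protocol's own 90%.

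**Conclusion.** The point holds as a defect of specification with a clear efficiency remedy. The analysis section commits to an unadjusted two-group test, does not tie it to the change score behind the sample size, and makes no use of baseline values that will be collected anyway. On change scores power is about 90%. On follow-up scores it falls below that if ρ exceeds 0.5, to between 79% and 28% for assumed raw SDs of 3 to 6. Which case applies cannot be settled from the document, so it would be wrong to report the trial as underpowered.

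The recommendation does not depend on settling it. Given the difference of 1.23, the SD of change of 2.59 and equal variances, ANCOVA gives about 91% to 96% power for raw SDs from 2.59 to 6, and matches or beats both unadjusted tests at every correlation checked. It also corrects for chance baseline imbalance, which a follow-up-score comparison ignores and a change-score comparison over-corrects when ρ is below 1. This should be changed, but it does not threaten the validity of the trial.

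**What to change.** In the Statistical analysis section, replace the unadjusted between-group t test for MOCA, MMSE and BI with wording such as: *The groups will be compared by analysis of covariance of the follow-up score, with treatment group as factor and the baseline score of the same scale as covariate; the adjusted mean difference will be reported with its 95% confidence interval.* A repeated-measures model with baseline as covariate is an acceptable alternative. In the Sample size section, add that 2.59 is an SD of change and that the 93 per group is therefore conservative for the adjusted analysis under the stated assumptions.

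If the investigators prefer to keep the t test, the least they should do is state that it is applied to change from baseline. That restores consistency with the sample size but forgoes the extra precision.

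The cost is wording: no new data, visits or patients. As recruitment began on 1 December 2019, the change should be recorded as a dated amendment before any outcome data are compared by group, through the ethics approval that the Quality control section requires for changes to the research plan.

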## Discussion

The effective improvement of cognitive impairment after stroke is particularly important to improve the rehabilitation and quality of life of patients after stroke, so it is necessary to take effective treatment measures to improve cognitive function. Acupuncture therapy has a history of more than 2000 years in China and has been widely used in Western countries in recent years. Our previous clinical research found that EA treatment at Baihui (GV20) and Shenting (GV24) along with NR on the head can effectively relieve cognitive impairment after stroke. However, the best acupuncture treatment mode and the cumulative effects of acupuncture still need further research and confirmation. Therefore, we propose a prospective, multicenter, large-sample randomized controlled trial to explore the cumulative effect of acupuncture and needle retention. This study is expected to provide a preliminary basis for the optimization of treatment methods for PSCI, to further develop a standardized, simple, effective, and easy-to-promote comprehensive TCM clinical rehabilitation treatment method.

Although most of the previous studies on acupuncture treatment of cognitive impairment used a combination of body acupuncture points and head acupoints [23–25], we will use only two acupuncture points on the head (GV20 and GV24) for treatment, which is based on the results of literature analysis and a continuation of previous research [26, 27]. In addition, unified acupuncture points may reduce variability and increase the accuracy and persuasiveness of this study. In recent years, the MMSE, MOCA, and BI scales have been used to assess various aspects of cognitive function, so we used these three items as outcome indicators to reduce the interference of subjective factors and simplify the assessment of cognitive impairment. In addition, the multicenter design of the study may introduce a bias, mainly by including differences between acupuncture operator techniques. Therefore, to eliminate the bias caused by operator inconsistency, we will conduct unified training for all the acupuncturists participating in this study and strictly regulate the acupuncture operation to maximize the elimination of this bias. However, although all results will be measured and recorded by independent researchers to minimize the risk of detection bias, as a limitation of this protocol, we cannot use double-blind procedures to conduct this study due to the nature of acupuncture treatment.

To achieve our clinical goals, we will strive to standardize every step of this study. We expect that this trial will provide strong evidence for acupuncture treatment of PSCI, with a view to incorporating or updating the corresponding TCM rehabilitation guidelines and further formulate a clinical rehabilitation treatment method suitable for grassroots promotion and application.

### Dissemination policy

After study completion, the researchers will submit the final data to the Henan Administration of Traditional Chinese Medicine in the form of a research report. The findings will be shared with healthcare professionals, the general public, and relevant organizations through the publication of manuscripts and conference presentations.

### Trial status

The recruitment of patients for this study began on 1 December 2019, and this study is ongoing. Protocol version number and date: V2.0, 1 September 2019. The recruitment of patients is expected to be completed in June 2021.

## Data Availability

Not applicable; no data have yet been generated.

## Abbreviations

BI: Barthel Index
CRF: Case report form
CT: Computed tomography
EA: Electroacupuncture
MMSE: Mini-Mental State Examination
MOCA: Montreal Cognitive Assessment scale
MRI: Magnetic resonance imaging
NR: Needle retention
PSCI: Post-stroke cognitive impairment
QOL: Quality of life
SOP: Standard operating procedure
TCM: Traditional Chinese medicine
